**Figure 1 F1:**
[figure not shown]
Research process. ALND, axillary lymph node dissection; BCS, breast-conserving surgery; CWI, chest wall irradiation; RI/RecurIndex, Recurrence Index; RNI, regional lymph node irradiation; RT, radiotherapy; SLNB, sentinel lymph node biopsy; WBI, whole breast irradiation.

Box 1Eligibility criteria for the studyInclusion criteriaAge ≥18 years, ≤70 years.Eastern Cooperative Oncology Group Performance Status ≤2 (online supplemental file 17).Postoperative pathology confirms the diagnosis of invasive breast cancer.Meets the clinical definition of low risk: (1) axillary lymph node micrometastasis (N1mic), or (2) N1 patients who meet all of the following conditions: (a) age ≥40 years; (b) lymphovascular invasion (LVI) negative or limited to individual or small foci of LVI (excluding extensive or large amounts of LVI); (c) three clinical molecular subtypes (luminal A type, luminal B1 type and luminal B2 type) are allowed in this study: oestrogen receptor (ER)-positive (ER ≥1%) and human epidermal growth factor receptor 2 (HER2)-negative or ER-positive (ER ≥1%) and HER2 overexpressing, respectively.Postoperative pathological diagnosis of axillary lymph node status as any of the following: (a) sentinel lymph node biopsy or axillary lymph node dissection with micrometastasis (N1mic), (b) sentinel lymph node biopsy with one to two lymph node macrometastases (N1sln), (c) sentinel lymph node biopsy+axillary lymph node dissection or simple axillary lymph node dissection with one to three lymph node metastases (N1).The primary tumour and breast underwent breast-conserving surgery or mastectomy±breast reconstruction (autologous/prosthetic).A thorough systemic examination (eg, chest X-ray, ultrasound, CT, etc) within 3 months before randomisation for radiotherapy must confirm no distant metastasis.Mammography and/or MRI within 12 months before surgery or randomisation for radiotherapy must confirm no contralateral breast cancer.Postoperative completion of at least four cycles of adjuvant chemotherapy containing anthracycline or taxane regimens.Radiotherapy must be performed sequentially after the completion of all adjuvant chemotherapy, starting no later than 8 weeks after the end of chemotherapy.Patients must have sufficient postoperative paraffin tissue sections of the primary tumour for Recurrence Index testing.No history of other malignant tumours, except for basal cell carcinoma of the skin.Signed informed consent before the start of the study.Exclusion criteriaConfirmed T3–4, N0, N2–3, M1 stage disease before postoperative radiotherapy enrolment.Received any neoadjuvant treatment before surgery, including chemotherapy, endocrine therapy, targeted therapy or radiotherapy.Patients who underwent mastectomy and only had sentinel lymph node biopsy.History of contralateral breast cancer or other second primary malignant tumour (excluding basal cell carcinoma of the skin and cervical carcinoma in situ).History of chest radiotherapy.Presence of severe heart, lung, liver, kidney, haematopoietic system or nervous system diseases, or mental disorders.Presence of scleroderma or active systemic lupus erythematosus or other autoimmune diseases.Pregnant and breastfeeding patients.

### Randomisation method

Stratified randomisation will be used for the randomised study. For the active postoperative radiotherapy trial involving the clinically low LRR risk but high RecurIndex-LRR risk population, participants will be stratified by N1 status, surgical method and enrolling hospital, and then randomised in a 1:1 ratio into the experimental and control groups.

Randomisation stratification factors are as follows:

N1 status: N1mic or one to two lymph node macrometastases (including N1sln), or three lymph node macrometastases.Surgical method: BCS or mastectomy.Multicentre enrolling hospital.

A central randomisation system was developed by TaiMei Medical Technology Company to facilitate the randomisation process. Statistical experts responsible for randomisation designed the randomisation parameters in advance, allowing the system to generate a random allocation table. The main clinical trial centres conduct eligibility screening for potential participants. Once deemed eligible, the researchers at each subcentre access the server via the internet and enter the information of the enrolled patients. The system then assigns a corresponding randomisation number based on the random allocation table, determining the patient’s placement in the respective study group.

### Participants and recruitment

Patients will be recruited by radiation oncologists from each participating research centre. For each interested patient, the clinician or clinical coordinator will provide a complete and comprehensive introduction to them or their designated representative, informing the patient about their rights, the risks involved and the potential benefits they may receive to enhance their compliance with the protocol. Prior to enrolment, patients are required to sign an informed consent form, which will be kept in the case report form (CRF). Patient registration is scheduled to begin on 1 April 2023 (see online supplemental file 1 for details), and is expected to continue for 5 years (tentatively until January 2028). The final collection of data for the primary outcome measures is anticipated to be completed by December 2032.

### Patient and public involvement

Neither patients nor the public were involved in the design, conduct, reporting or dissemination plans of this study.

### Objectives and endpoints

This study aims to evaluate whether adjuvant radiotherapy to the regional lymph nodes after BCS or chest wall plus regional lymph node radiotherapy after total mastectomy can further improve clinical outcomes in N1 patients with low clinical risk but high RecurIndex-LRR risk.

The primary endpoint is invasive disease-free survival (IDFS). Secondary endpoints are AFR, LRR-free survival (LRFS), DMFS, RFS, OS, DFS, BCSM and patient quality of life assessment. The specific definitions can be found in table 1.

**Table 1 T1:** The specific definitions of the study endpoints

IDFS	The time from the day the subject is randomised to the earliest occurrence of invasive cancer local recurrence, distant metastasis or death, but does not include contralateral breast second primary cancer.
AFR	Any ipsilateral chest wall, breast, regional lymph node recurrence or distant metastasis event that occurs during the follow-up period.
LRFS	The time from the day the subject is randomised to the earliest occurrence of ipsilateral chest wall, breast, or regional lymph node recurrence or death.
DMFS	The time from the day the subject is randomised to the earliest occurrence of distant metastasis or death.
RFS	The time from the day the subject is randomised to the earliest occurrence of ipsilateral chest wall, breast, regional lymph node recurrence, distant metastasis or death.
OS	The time from the day the subject is randomised until the patient’s death.
DFS	The time from the day the subject is randomised to the recurrence of the disease or the patient’s death due to disease progression.
BCSM	The time from the day the subject is randomised to death from breast cancer.

AFRany first recurrenceBCSMbreast cancer-specific mortalityDFSdisease-free survivalDMFSdistant metastasis-free survivalIDFSinvasive disease-free survivalLRFSlocal–regional recurrence-free survivalOSoverall survivalRFSrecurrence-free survival

During the screening period and 3 months after the end of treatment, patients in each group fill out the quality of life questionnaire (EORTC Core Quality of Life Questionnaire (EORTC QLQ-C30)), as well as the breast cancer survival quality scale (EORTC Breast Cancer-Specific Quality of Life Questionnaire (EORTC QLQ-BS23)) annually during the follow-up phase (onlinesupplemental files 2  3).

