**Methods and analysis:**

The RIGAIN (RecurIndex-Guided postoperative radiotherapy with or without Avoidance of Irradiation of regional Nodes in 1–3 node-positive breast cancer) Study is a multicentre, prospective, randomised, open-label, phase III clinical trial that is being conducted in China. In this study, patients with low clinical LRR risk but high RecurIndex-LRR risk are randomly assigned in a 1:1 ratio to the experimental group or the control group. In the experimental group, RNI is performed and the control group omits RNI. Efficacy and safety analyses will be conducted, enrolling a total of 540 patients (270 per group). The primary endpoint is invasive disease-free survival, and secondary endpoints include any first recurrence, LRR-free survival, distant metastasis-free survival, recurrence-free survival, overall survival, disease-free survival, breast cancer-specific mortality and assessment of patient quality of life. The study began in April 2023 and with a follow-up period of 60 months after the last participant completes radiation therapy.

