## Materials and methods

The RIGAIN (RecurIndex-Guided postoperative radiotherapy with or without Avoidance of Irradiation of regional Nodes in 1–3 node-positive breast cancer) Study is a multicentre, prospective, randomised, open-label, phase III clinical trial that is being conducted in China. The overall research process is illustrated in figure 1. This study aims to screen postoperative patients with early-stage breast cancer (pT1–2N1M0) who have completed standard systemic therapy and possess eligible pathological specimens for participation. The inclusion and exclusion criteria are listed in box 1. RecurIndex testing will be performed using postoperative paraffin-embedded tissue sections from the primary lesion. The study is divided into a randomised controlled trial and an observational study based on clinical risk and RecurIndex-LRR risk. Patients with low clinical risk but high RecurIndex-LRR risk will be randomly assigned in a 1:1 ratio to either the experimental group (RNI) or the control group (no RNI), while patients with low clinical risk and low RecurIndex-LRR risk will be included in the observational study. This article primarily focuses on the randomised controlled trial. The study participants will receive the following treatments: experimental group: for patients who underwent BCS, RNI will be performed in combination with whole breast irradiation (WBI)+tumour bed boost irradiation. For patients who underwent mastectomy, chest wall irradiation (CWI) will be administered in combination with RNI. Control group: RNI will be omitted. For patients who underwent BCS, only WBI+tumour bed boost irradiation will be administered. For patients who underwent mastectomy, both RNI and CWI will be omitted. A comparative effectiveness analysis will be conducted. The study commenced in April 2023.

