### Safety assessment indicators

All patients participating in the RIGAIN Study are required to undergo safety assessments, including acute radiation reactions and late radiation injuries for radiotherapy patients. The evaluation criteria and handling of injuries are detailed in onlinesupplemental files 4^7^. Their treatment is shown in online supplemental file 8, including acute skin reactions to radiotherapy, symptomatic radiation pneumonitis, long-term cosmetic outcomes (BCS/reconstruction patients), skin fibrosis (total mastectomy patients), ischaemic heart disease, upper limb oedema,^27 28^ brachial plexus injury and second primary tumour.^29^

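### The primary endpoint definition does not say whether a regional nodal recurrence counts, in a trial of regional nodal irradiation

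*Protocol article*

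**What the plan says.** The Objectives and endpoints section names IDFS as primary and refers the reader to Table 1 for the definitions, so the table is the operative text. The relevant rows are:

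- IDFS (primary): "earliest occurrence of invasive cancer local recurrence, distant metastasis or death, but does not include contralateral breast second primary cancer".
- RFS: "earliest occurrence of ipsilateral chest wall, breast, regional lymph node recurrence, distant metastasis or death".
- LRFS: "earliest occurrence of ipsilateral chest wall, breast, or regional lymph node recurrence or death".
- AFR: "Any ipsilateral chest wall, breast, regional lymph node recurrence or distant metastasis event that occurs during the follow-up period".

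The abstract gives the randomised contrast: "In the experimental group, RNI is performed and the control group omits RNI". Under Materials and methods, both arms receive whole breast irradiation and a tumour bed boost after breast-conserving surgery. For mastectomy patients in the control arm the text reads: "For patients who underwent mastectomy, both RNI and CWI will be omitted".

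The Sample size estimation section plans on 5-year IDFS of 89% against 82% (HR 0.587). It does not say whether those rates count nodal recurrence.

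**The concern.** Three rows of Table 1 name the regional nodes and the primary endpoint row does not. Someone applying the table as written would take that difference as meaningful and would not record an isolated nodal relapse as an IDFS event.

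That matters more here than in most breast cancer trials. After breast-conserving surgery, RNI is the only radiotherapy difference between the arms, and patients are selected for high local–regional recurrence risk. Under the literal reading, the primary endpoint leaves out relapse at the site being irradiated. If the planning rates do include such relapses, the endpoint actually analysed would have fewer events and, where RNI prevents nodal relapse better than it prevents other events, a hazard ratio closer to 1 than the plan assumes.

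**Working it through.** **Comparison of the definitions (Table 1)**

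| Endpoint | Breast / chest wall | Regional nodes | Distant | Death |
|---|---|---|---|---|
| IDFS (primary) | invasive local recurrence | not named | yes | yes |
| RFS | named | named | yes | yes |
| LRFS | named | named | no | yes |
| AFR | named | named | yes | no |

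No section states that *local* in the IDFS row covers the nodes. The closest indication is the last paragraph of the Introduction, which pairs local recurrence with distant metastasis when it describes the risks to be evaluated. In a study built on local–regional risk, that looks like shorthand for local–regional recurrence. The row is therefore ambiguous. The comparison does not show a deliberate exclusion.

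**Plan's own figures**

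- HR = ln(0.89)/ln(0.82) = 0.587, which matches the article.
- 216/0.8 = 270 per group, 540 in total, which also matches.
- The 216 per group does not reproduce under the model below, which needs 267. That is a separate matter, and the 540-patient, no-dropout case serves here only as a common reference.

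**Model**

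- Exponential survival with hazard λ = −ln(S)/5, where S is 5-year IDFS.
- Uniform accrual over 5 years plus 5 years of follow-up (Sample size estimation), so the event probability is p = 1 − [exp(−5λ) − exp(−10λ)]/(5λ).
- Events D = 270 × (p_E + p_C).
- Power = Φ(√D/2 × |ln HR| − 1.96), the Schoenfeld formula at one-sided 0.025.

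**Baseline**

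- λ_E = 0.02331 and λ_C = 0.03969, so p_E = 0.160 and p_C = 0.256.
- D = 270 × 0.416 = 112.4.
- Power = Φ(5.300 × 0.532 − 1.96) = Φ(0.86) = 81%.

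**Illustration of the literal reading**

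Let r be the part of the 18% control 5-year risk that is isolated nodal recurrence, and v the share of it that RNI prevents. If the planning rates include these events and the endpoint does not count them, then S_C = 0.82 + r and S_E = 0.89 + (1 − v)r. Both r and v are assumptions. For scale only, the Introduction gives a 5-year rate of 7% for all local–regional recurrence in RecurIndex-high patients, not split by site.

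| r | v | S_C | S_E | HR | Events (540) | Power |
|---|---|---|---|---|---|---|
| 0 | – | 82.0% | 89.0% | 0.587 | 112 | 81% |
| 1 point | 50% | 83.0% | 89.5% | 0.595 | 107 | 76% |
| 2 points | 50% | 84.0% | 90.0% | 0.604 | 101 | 72% |
| 3 points | 50% | 85.0% | 90.5% | 0.614 | 96 | 66% |
| 1 point | 75% | 83.0% | 89.25% | 0.610 | 108 | 73% |
| 2 points | 75% | 84.0% | 89.5% | 0.636 | 103 | 63% |
| 3 points | 75% | 85.0% | 89.75% | 0.665 | 98 | 52% |

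The table assumes that an uncounted patient never becomes an IDFS event. A nodal relapse followed by distant metastasis or death would still be counted, only later. If half of the uncounted patients have a counted event within the 5-year risk, r is in effect halved. At v = 75% the range of 73%–52% then becomes about 77%–68%. That relies on follow-up continuing after nodal relapse. The Follow-up evaluation section schedules check-ups until an endpoint event and does not say which endpoint is meant.

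**The case against.** The strongest reply is that the literal reading is not what the investigators meant. The Introduction appears to use local recurrence for local–regional recurrence, and a trial of nodal irradiation would hardly leave out nodal relapse on purpose. The article is also a condensed account, and the full protocol or eCRF instructions may settle the matter. The point about intent stands, so the article should not be read as showing a deliberate exclusion. It does not clear the wording, because Table 1 is presented as the place where the endpoints are defined and spells out the nodes in three other rows.

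The second reply is that the power loss rests on assumptions. That stands in full. The article gives neither an isolated nodal rate nor an RNI effect on it, and if 89% and 82% were set on the Table 1 wording, nothing is lost against plan.

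A reader might also draw three further criticisms from these passages, none of which is supported:

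- **Contralateral cancer.** The IDFS row excludes it openly, and Safety assessment indicators tracks "brachial plexus injury and second primary tumour". This is a stated choice, with the harm recorded elsewhere.
- **RFS as a redundant endpoint.** Even if *local* includes the nodes, IDFS requires invasive recurrence and the RFS row does not. Overlap between a primary and a secondary endpoint is no defect.
- **Biased coding between centres.** The trial is open-label, but nothing shows that centres code differently. The Data management section provides source verification by monitors and an independent committee that reviews recurrences and metastases.

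**Conclusion.** The point holds as an ambiguity in the primary endpoint. As written, the IDFS row does not count an isolated regional nodal recurrence, three neighbouring rows name it, and no text resolves the difference.

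It would go too far to conclude that the trial has lost a known amount of power. The fall from 81% to 76%–66% (half prevented) or 73%–52% (three quarters prevented) rests on four assumptions: 1 to 3 points of isolated nodal risk, the stated share prevented, planning rates that include those events, and no later counted event in the same patients. The lower figures are the extreme of that range.

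The point is still worth settling because it determines what the primary analysis counts and costs almost nothing to resolve. The article expects enrolment until about January 2028 and final primary outcome data by December 2032, so there is time to do so before analysis.

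**What to change.** 1. Reword the IDFS row of Table 1 as the time from randomisation to the first of: invasive ipsilateral breast or chest-wall recurrence, invasive regional lymph node recurrence, distant metastasis, or death from any cause. The stated exclusion of contralateral second primary breast cancer can remain.
2. Align the eCRF event coding with that wording.
3. State in the Sample size estimation section that the 89% and 82% rates use the same definition. If they do not, restate the rates and the hazard ratio.

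The cost is one definition, one coding instruction and one sentence of confirmation, submitted for Ethics Committee approval as the article requires for any protocol modification. No new data are needed, since nodal recurrence is already required for AFR, LRFS and RFS.

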### RecurIndex test

RecurIndex testing was performed using postoperative paraffin-embedded tissue sections from the primary lesion of the subjects. All sections were uniformly sent to the Jiangsu Simcere Pharmaceutical Co, Jiangsu Simcere Diagnostics Co for free testing. Formalin-fixed, paraffin-embedded tissue blocks should be selected that cover the largest amount of tumour cells and meet the diagnostic criteria in appearance. Tissue sections with an excess amount of normal tissue, necrotic tissue, adipose tissue or haemorrhagic tissue should not be sent for examination. The tumour cell content in the identified sections should be >50% for the test to be performed. A total of 10 consecutive sections are needed, each with a thickness of 5 µm. The sections can remain unstained and without coverslips. There is no need to oven-dry the sections; they can be air-dried naturally.

### Safety assessment indicators

All patients participating in the RIGAIN Study are required to undergo safety assessments, including acute radiation reactions and late radiation injuries for radiotherapy patients. The evaluation criteria and handling of injuries are detailed in onlinesupplemental files 4^7^. Their treatment is shown in online supplemental file 8, including acute skin reactions to radiotherapy, symptomatic radiation pneumonitis, long-term cosmetic outcomes (BCS/reconstruction patients), skin fibrosis (total mastectomy patients), ischaemic heart disease, upper limb oedema,^27 28^ brachial plexus injury and second primary tumour.^29^

### Radiotherapy

#### General consideration

The overall treatment plan for each participant is determined by the researchers at the corresponding subcentre based on the participant’s condition. Depending on their assigned group, patients will either undergo RNI or be exempted from it. Breast-conserving patients will all receive WBI. Patients should start radiotherapy within 8 weeks after completion of adjuvant chemotherapy. The regional lymph nodes include the supraclavicular lymph nodes and infraclavicular lymph nodes (unresected levels II/III axillary lymph nodes), with or without internal mammary lymph nodes (at least from the first to the third intercostal space). For patients with minimally positive sentinel lymph node and without axillary lymph node dissection, the inclusion criteria encompass the low/intermediate axillary lymph nodes. The planned endocrine therapy and anti-human epidermal growth factor receptor 2 (HER2) treatment can be continued during the radiotherapy process.

#### Patient positioning and immobilisation

The patient lies on a fixed device such as a breast support, vacuum bag or foam pad. A CT scan is performed with a thickness of 3–5 mm, from the second cervical vertebra to the second lumbar vertebra. CT positioning includes surface marking, where lead wires are placed on the surgical scar of the primary lesion in breast-conserving patients or the chest wall scar in total mastectomy patients, as well as on the scar of the axillary sentinel/clearance lymph node incision. If there is a drainage site, it should also be separately marked with a lead wire or lead point.

#### Volumes of interest

The clinical target volume (CTV) and organs at risk (OARs) must be delineated on all CT slices, following the contouring guidelines of the Radiation Therapy Oncology Group (RTOG) and considering the actual situation at each CT slice. Detailed descriptions of CTV and OARs can be found in online supplemental file 9. The margin between the planning target volume (PTV) and CTV depends on the institutional standards of each participating centre, with a recommended minimum of 5 mm. Contours should be drawn according to the RTOG guidelines, including the ipsilateral and contralateral lungs, heart, humeral heads and spinal cord.

